**Abstract**

People in custody are at high risk of developing depression. Accessing psychological treatments such as Cognitive Behavioural Therapy (CBT) in a prison setting is a particular challenge in part due to difficulties in accessing specialist mental health workers. An alternative treatment, Behavioural Activation (BA), is just as effective as CBT for depression in adults who are not in prison settings. BA works by teaching people the skills to notice fluctuations in their mood and notice behaviours they were engaging in. The second step is to help people schedule activity which results in an increase in mood. The application of BA may increase access to effective treatment for people in custody with depression. However, we lack trial data concerning its acceptability and feasibility. The aim of the study is to examine the feasibility and acceptability of telehealth BA plus usual prison health care. Findings from the study may provide opportunities for scaling up BA to support people in custody living with depression.

**Method**

A sample of 60 people in custody aged over 18 years or older with presenting symptoms of depression as assessed using the PHQ 9 scale (with a score of 5-14 mild to moderate depression) will participate in the trial. Recruited people in custody will be randomised to receive BA plus treatment as usual (TAU) or TAU for depression provided by custodial health nurses. Eight custodial health nurses will be recruited from four rural prisons in South Australia. The custodial health nurses will be prepared to deliver Behavioural Activation to people in custody at the selected prisons. The BA intervention will involve preparing people in custody to monitor their mood, identify triggers that can impact mood, identify activities that may enhance mood, and enable each participating person in custody to formulate an activity schedule. BA will involve twelve conversations with people in custody held twice weekly over six weeks. Changes in depressive symptoms and health-related quality of life will be assessed at three-time points: (a) at baseline, (b) 6 weeks, and (c) 3 months post-intervention. We will use descriptive statistics to report changes over time, but not make any judgement. In addition, we will interview custodial health nurses and people in custody to understand further BA acceptability and feasibility in prison settings.

**Discussion**

The findings will inform the design of a full-scale randomised controlled trial to test the efficacy of co-delivered tele-trial BA for people in custody with depression.

**Trial registration**

Australian New Zealand Clinical Trials Registry (ACTRN12623000346673p)

**BACKGROUND**

People in custody are at an increased risk of developing mental health problems, particularly depression (1-3). In a systematic review of 109 studies involving 33, 588 people in custody conducted in 24 countries during the period 1966 to 2010, the authors reported a pooled prevalence of major depression of 10.2% (95% CI 8.8–11.7) in male and 14.1% (95% CI 10.2–18.1) in female people in custody (4). Depression is often underdiagnosed and under-treated in prison settings (1). Treating depression in people in custody can have several economic and social benefits. For instance, treating depression in people in custody reduces the risks of suicide (5) and self-harm (6) whilst in custody and premature mortality (7), recidivism (8), and violence and victimisation (1) on release from prison.

The recommended treatments for depression include antidepressant medication and psychotherapy used singly or in combination (9). However, the use of antidepressants in custodial settings is problematic such as problems with adherence to antidepressants or misuse and adverse effects (10). CBT is the recommended treatment for depression in adults (9). CBT is effective in treating depression in people in custody (11, 12). However, accessing CBT in prison health care environments is challenging. Typically, you need to be a specialist mental health worker (Psychologist, Occupational Therapist, or Mental Health Nurse) to deliver BA. Accessing these types of specialist mental health workers in prisons is challenging. An alternative psychotherapy to CBT is Behavioural Activation (BA). A comparison of the effectiveness of CBT and BA in the treatment of depression indicated that both psychotherapies are equally effective (13). BA is a derivative of CBT but works as a standalone psychotherapy. BA works by teaching people the skills to notice fluctuations in their mood and notice behaviours they were engaging in. The second step is to help people schedule activity which results in an increase in mood. A strength of BA is you do not need to be a specialist mental health worker and training health care workers to practice the approach involves a relatively short – five days – in comparison to CBT – 18 months. The theoretical underpinning of BA is that people improve their mood if they routinely engaged in pleasurable events and minimised avoidance (14, 15).

We do not yet understand if BA is efficacious in treating depression in adult people in custody when delivered by non-specialist mental health workers. This clinical trial will investigate the feasibility of preparing custodial health care nurses to deliver BA to support people in custody with depression. If the clinical trial demonstrates that BA delivered by custodial health nurses is efficacious in treating depression in people in custody, this may help to increase access to evidence-based psychological treatment for people in custody living with depression.

**AIMS**

We will examine the feasibility and acceptability of:

1. Telehealth BA plus usual SA prison health care (intervention) compared to usual SA prison health care alone (treatment as usual (TAU)) in the treatment and management of depression in people in custody who have been diagnosed with a mood disorder.
2. Telehealth BA plus usual SA prison health care (intervention) compared to usual SA prison health care alone (TAU) in improving the quality of life of people in custody who are diagnosed with clinically meaningful depressive symptoms.

**Objectives**

**Custodial health nurses**

1. Establish custodial health nurses' fidelity to BA treatment.
2. Explore custodial health nurses' experiences of delivering BA treatment to people in custody supported by telehealth.
3. Explore the custodial health nurses' experiences receiving co-delivered tele-trial BA training and supervision.

**People in custody**

1. Establish the number of people in custody accessing the South Australian Prison Health Service (SAPHS) who report experiencing clinically meaningful depressive symptoms.
2. Determine the number of people in custody with clinically meaningful depressive symptoms who are approached and agree to participate in the trial.
3. Determine the proportion of eligible people in custody who have agreed to participate and agree to be randomised.
4. Determine the proportion of people in custody with clinically meaningful depressive symptoms that participate in the trial who complete baseline measures.
5. Determine the proportion of people in custody who complete a co-delivered telehealth BA treatment (attending for a minimum of six sessions over six weeks)
6. Determine the proportion of people in custody who complete outcome measures at six weeks and three-month follow-up.
7. Calculate the preliminary efficacy of BA on depressive symptoms (primary outcome) and improving health-related quality of life (secondary outcome).
8. Explore people in custody's experiences of receiving a co-delivered telehealth BA.
9. Report the number of adverse events and harms that occur during the trial.

**METHOD**

**Design**

We will evaluate the feasibility and acceptability of BA plus usual SA prison health care in reducing depressive symptoms in people in custody compared to SA prison health care alone (TAU). The design of this protocol is informed by the Standard Protocol Items: Recommendations for Interventional Studies (SPIRIT 2013) statement: defining standard protocol items for clinical trials (16). The Consolidated Standards of Reporting Trials (CONSORT) guidelines will guide reporting of the trial. Consolidated criteria for Reporting Qualitative research (COREQ) guidelines will be followed for the reporting of findings from interviews or focus groups (17, 18).

**Setting**

Our feasibility trial will be implemented across a cluster of four South Australian prison sites (Murray Bridge, Port Augusta, Port Lincoln, and Cadell) in which primary health care services are provided by Central Adelaide Local Health Network (through Prison Health Services) to people in custody. (Figure 1).

Figure 1 Tele trial cluster

**Participants**

***Inclusion criteria***

The study will comprise two groups of participants: Custodial health nurses and people in custody with depressive symptoms.

1. Custodial health nurses:
2. employed by CALHN
3. Complete the Professional Certificate in Behavioural Activation
4. agree to participate in the study.
5. People in custody that are:
6. Aged 18 years or above.
7. Receiving a primary health care service by SA health nurses provided by CALHN at any of the four participating prison sites.
8. Experiencing mild to moderate depressive symptoms as demonstrated with a baseline score of 5-14 (mild to moderate depression) (19) on the PHQ-9 scale.
9. Understand, read, write, and speak English.
10. Provide informed consent.

Prior or current use of medication or psychotherapy will not be a precluding factor.

***Exclusion criteria***

- People in custody with depressive symptoms who achieve a baseline score of 15+ on the PHQ-9 scale will be excluded from the study for their safety.
- People in custody who express suicidal ideation or present a risk to themselves, or others will be excluded. These potential participants who are excluded will be referred to a general practitioner or mental health professional for support. People in custody will be excluded if they display acute depression and need to be seen by a psychiatrist.
- People in custody with multiple mental health diagnoses.
- A Department for Corrections (DCS) Notice of Concern (NOC) and placed for High-Risk Assessment Team (HRAT) review.
- People in custody who are at risk of self-harm, suicide, or homicide.
- People in custody who are actively being treated by Mental Health or Forensic Mental Health team.

**Sample size**

Our target sample size is 60 people in custody and eight (8) custodial health nurses. We will determine the sample size estimation based on the median sample size per arm of 30 recommended for feasibility studies with continuous outcome measures such as levels of depressive symptoms (20).

**Recruitment**

1. Custodial health nurses

Initial contact with the custodial health nurses who complete the BA training will be made via email by PI MJ (See Attachment VI). If the custodial health nurse expresses an interest in participating in the trial, the tele-trial nurse will contact potential participants via email, providing an information sheet about the research and a consent form. The tele-trial nurse will be available to answer participant questions via email or phone. The tele-trial nurse will follow up with the potential participant after one week to establish whether the custodial health nurse is willing to participate in the research and return the signed consent form. The custodial health nurse can withdraw from the study at any time.

The tele-trial nurse is employed by South Australia Regional Tele Trials Scheme and is not an employee of the South Australia Prison Health Service. The role of the tele-trial nurse is to support the Principal Investigator to conduct a clinical trial geographically remote from the Principal Investigator’s primary site. They will work collaboratively with the site-specific staff of the SAPHS to identify and recruit potential participants. In addition, the tele-trial nurse will be responsible for data collection including key outcome measures and interviews.

1. People in custody

Preliminary identification of the potential people in custody will be done by the custodial health nurses. The custodial health nurses will screen if the people in custody meet the eligibility criteria set for the clinical trial. The nurses will briefly inform the people in custody about the study and offer them an information sheet. Consenting people in custody will be approached by the research tele-trial nurse. The research tele-trial nurse will then assess if the people in custody meet the inclusion criteria including experiencing depressive symptoms before handing out a detailed study information sheet. The research tele-trial nurse will offer further explanation or clarification as required and address concerns the people in custody may have. The people in custody will be given at least 48 hours to consider their involvement with the study.

At the end of the study, we will invite a sub-sample of custodial health nurses and people in custody to participate in individual, semi-structured interviews. Four to six custodial health nurses and 10 to 20 people in custody will be interviewed. The research tele-trial nurse will contact the custodial health nurses and the people in custody about the interviews.

**Random treatment allocation and blinding**

The research tele-trial nurse will collect baseline data from the people in custody who voluntarily agree to participate in the study. The people in custody will then be randomly assigned into either: 1) the Behavioural Activation group, which will receive BA plus usual prison health care, or 2) the TAU group, which will receive the usual prison health care alone.

An external computerised randomisation service will be contracted to generate random allocation. Block randomisation with random permuted block sizes will ensure appropriate allocation concealment and equal sample sizes across groups. Following baseline data collection from consenting people in custody, the research trial nurse will insert the unique participant ID into the online randomisation service (sealedenvelope.com) and receive an email confirmation of their group allocation. The allocation sequence is retained by the contracted service and the research trial nurse will be unaware of group allocation until receiving confirmation for each participant. The tele-trial research nurse will then inform the people in custody and the custodial health nurses of treatment allocation. Allocation will be blinded to the data manager/statistician, but it will not be masked to the custodial health nurses and research trial nurse who will collect the baseline, post-intervention, and follow-up outcome data.

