**Intervention**

**BA tele-trial intervention group**

We will recruit approximately 30 people in custody in the intervention group who will receive BA plus usual prison health care (20). The intervention will be delivered by the custodial health nurses who will receive ongoing clinical supervision from an expert in BA via a telehealth video link. The people in custody will be offered twelve sessions of BA, which will be delivered twice weekly, in 30-minute sessions, for six weeks. Specific BA techniques that will be applied include (a) identification of depressed behaviours (b) analysis of the triggers and consequences of depressed behaviours (c) monitoring of activities (d) development of alternative goal-orientated behaviours (e) scheduling of activities, and (f) the development of alternative behavioural responses to rumination.

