**Statistical analyses**

All data will be entered and analysed descriptively. The primary analysis is intended to determine whether conducting a subsequent fully powered RCT is feasible. Therefore, the analyses will be descriptive by exploring all feasibility outcomes and will include measures of uncertainty, such as 95% CIs. As feasibility trials are not designed to establish efficacy, we will estimate the variance of outcome measures and calculate the effect size differences (with 95% CIs) on outcome measures from baseline to both follow-up points (on an intention-to-treat basis) in both groups. Where appropriate, the generalised estimating equation (GEE) will be employed to analyse the preliminary effects of BA across the two time points (baseline and 6 weeks). The GEE analysis will account for intra-correlated repeated outcome data and accommodate data missing at random.

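### Permuted-block randomisation across four prisons is described without stratification by prison, so arm sizes within a prison, and the BA caseload there, are left to chance

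*Protocol*

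**What the plan says.** The allocation section of the protocol (Random treatment allocation and blinding) is fairly specific. It states that "Block randomisation with random permuted block sizes will ensure appropriate allocation concealment and equal sample sizes across groups". It also says that, after baseline, "the research trial nurse will insert the unique participant ID into the online randomisation service", and that the contracted service keeps the sequence. No stratification factor is named, and no entry of site is described.

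The trial is "implemented across a cluster of four South Australian prison sites" (Setting). The target is given in these words: "Our target sample size is 60 people in custody and eight (8) custodial health nurses" (Sample size), with 30 per arm. On delivery, the protocol says: "The intervention will be delivered by the custodial health nurses" (BA tele-trial intervention group), and the abstract's Method section has these nurses recruited from the four prisons. Under Contextual factors, the protocol plans to record organisational and staffing changes by site. Under Limitations, it expects lockdowns, staff shortages and limited therapy space. The Anticipated timeline gives one recruitment window, November to December 2023, with BA delivery from January 2024.

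On analysis, the only correlation mentioned is within person: "The GEE analysis will account for intra-correlated repeated outcome data and accommodate data missing at random" (Statistical analyses).

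**The concern.** A protocol normally fixes the stratification factors itself, because they must be set before the first allocation and cannot be added in an analysis plan. A single blocked list controls the running total across all four prisons. It does not control how the arms fall inside any one prison when participants from different prisons follow each other on the list.

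The comparison stays unbiased, so what is at stake is practical. BA sessions are delivered locally, and completion of BA is a main feasibility outcome. A prison that by chance receives ten BA participants has twice the delivery work of one that receives five. If that affects attendance, the completion proportion partly reflects how allocation happened to fall. Some precision is also lost when prisons differ in outcome and neither the design nor the analysis uses that.

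**Working it through.** **Inputs from the protocol.** 60 people, 30 per arm, four prisons (mean 60/4 = 15 each), eight nurses, permuted blocks with unstated sizes. The plan's own figure reproduces: 2 x 30 = 60. It rests on a rule of thumb ("median sample size per arm of 30 recommended for feasibility studies"), so there is no power calculation to check.

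**Assumptions, because the protocol gives no figure.** Block sizes 2/4/6, 4/6 or 4/6/8; prison sizes 15 each or 24/18/12/6; enrolment order from fully interleaved to strictly sequential.

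**1. One prison, interleaved enrolment.** The BA count among 15 people drawn from 60 with 30 BA is approximately hypergeometric:

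P(10:5 or worse) = 2 x sum over k = 10 to 15 of C(30,k) C(30,15-k) / C(60,15) = 0.233.

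For 11:4 or worse it is 0.072.

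**2. At least one of four prisons, by simulation (10,000 trials per scenario).**

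| Scenario, 15 per prison | Any prison 10:5 or worse | Mean within-prison difference |
|---|---|---|
| One list, interleaved | 58-59% | 2.75 |
| One list, prisons in sequence | 0.5-2.2% | 1.2-1.3 |
| Blocks stratified by prison | none seen (largest difference 3) | about 1.0 |

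Between the extremes, with blocks of 4 and 6 and prisons visited in random order, randomising 2, 3 or 5 people per visit gives roughly 46%, 38% and 19%. Other block sizes move these by several points. With prison sizes 24/18/12/6 and interleaving, some prison has an arm difference of 5 or more in 35-36% of trials. With stratified blocks none did.

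**3. Overall balance.** With one list the total arm difference stayed between 0 and 4 under every block set tried.

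**4. Precision.** In a prison-adjusted comparison, information is proportional to the sum of n1 x n0 / (n1 + n0) over prisons.
- Four prisons at 7:8 give 4 x 56/15 = 14.93.
- A pattern of 10:5, 7:8, 7:8 and 6:9 (30 BA in total) gives (50 + 56 + 56 + 54)/15 = 14.40.
- SE ratio = sqrt(14.93/14.40) = 1.018, so the imbalance alone costs about 2%.

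Adjusting for prison multiplies the SE by about sqrt(1 - ICC), which is 0.995, 0.975 and 0.949 for an assumed prison ICC of 0.01, 0.05 and 0.10.

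**5. Caseload.** At two sessions per person per week, ten concurrent BA participants mean 20 sessions a week in that prison, and five mean 10.

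**6. Nurse clustering, as a side note.** BA-arm design effect = 1 + (m - 1) x ICC; SE ratio for the arm difference = sqrt((1 + design effect)/2), with no nurse clustering in TAU.
- m = 30/8 = 3.75: ICC 0.01 to 0.10 gives design effect 1.03 to 1.28 and SE ratio 1.007 to 1.067.
- m = 5: design effect 1.04 to 1.40 and SE ratio 1.010 to 1.095.

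Both caseloads are shown because the BA training section sets a minimum of five BA participants per nurse. That implies at least 8 x 5 = 40, which does not fit about 30 in the BA arm. Those statements need reconciling.

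**The case against.** The strongest reply is that the protocol is silent, not wrong. It does not say the list is unstratified, and site can be configured in the service without being mentioned. That is fair, and the point is worded accordingly. But the section gives the method, the service and the input in detail, and run as written it is a single list.

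Several stronger readings are tempting and do not stand:

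- **That the claim of equal sample sizes is false.** It refers to the two arms overall, as the TAU group section confirms by giving 30 across sites. The simulation supports it.
- **That prison becomes confounded with arm.** Chance imbalance under concealed randomisation costs precision; it is not bias.
- **That usual care differs between prisons.** The protocol does not say so. The Setting section has one network providing primary care at all four.
- **That nurses would be overloaded.** No capacity and no number of nurses per prison is stated. With two per prison (an assumption), ten BA participants would be five each, which is the protocol's own minimum.
- **That the analysis ignores prison and nurse.** Such terms may sit in an analysis plan that is not at hand. Custodial nurses also provide TAU according to the abstract, so part of any nurse effect may be shared by both arms.
- **That imbalance is near certain.** The 58% needs full interleaving and nearly disappears with strictly sequential enrolment. The protocol plans no such sequence, but it does not exclude clumping.

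For very small prisons stratification helps less. With sizes 24/18/12/6, some prison still has a split of two-thirds or worse in about 16-28% of trials even when stratified, typically 4:2 in the prison of six.

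**Conclusion.** The point holds as a cheap design improvement. No stratification by prison is described in a four-prison trial with local delivery and expected site disruption. A 10:5 or worse split in at least one prison then has a probability of about 58% with equal prisons and interleaved enrolment, falling to 0.5-2.2% if prisons enrol in sequence. These figures rest on assumed prison sizes, block sizes and enrolment order.

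The consequences are modest: about 2% in the SE for the example pattern, and an uneven BA caseload that can affect the completion proportion. The randomised comparison remains valid and the overall arms near equal. If BA-arm intervals take no account of nurse clustering, the SE of the arm difference is understated by roughly 1-10% for an assumed ICC of 0.01-0.10. In a descriptive feasibility trial that deserves a remark and no more.

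**What to change.** In Random treatment allocation and blinding, state that randomisation is 1:1 and stratified by prison, using random permuted blocks whose sizes are held by the external service and not given in the protocol. The sizes should stay out because the Dissemination section plans to publish the protocol. The same sentence could credit concealment to the service that holds the sequence, since blocking does not provide it.

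In Statistical analyses, include prison, as the stratification factor, as a covariate in the GEE, and report the feasibility proportions by prison as well as overall. A note that nurse clustering in the BA arm may make intervals slightly too narrow is enough.

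**Cost.** A setting in the contracted service, three extra model parameters for four prisons, and one additional table. Allocations within a prison become slightly easier for unmasked staff to guess, which random undisclosed block sizes limit. Incomplete blocks in four strata may move the total slightly away from 30:30.

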**Preliminary intervention effects (primary and secondary outcomes)**

**Clinical outcome measure- depression**

The first clinical outcome will be a change in depressive symptoms as assessed by the tele-trial research nurse using the PHQ-9 scale.

*Primary Health Questionnaire Nine (PHQ 9)*. Depressive symptoms will be measured with the Primary Health Questionnaire Nine (PHQ 9) (21, 22). The PHQ 9 is a 4-point Likert-type scale (0, absent; 1, mild; 2, moderate; 3, severe) with nine items that correspond to the DSM-IV Diagnostic Criterion A symptoms for major depressive disorder (23). A meta-analysis rated the PHQ-9 scale as being reliable with a sensitivity of 88% and a specificity of 78% at a cut-off of 10 or above (24).

The clinical outcome measure will be implemented at three-time points (a) at baseline (0 weeks), (b) at 6 weeks post-intervention, and (c) at 3 months post-intervention.

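### The nurse who assesses the outcomes also receives and announces every allocation, which is the main avoidable source of assessor unmasking

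*Protocol*

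**What the plan says.** Random treatment allocation and blinding sets out the sequence. After collecting baseline data, the trial nurse is to "insert the unique participant ID into the online randomisation service (sealedenvelope.com) and receive an email confirmation of their group allocation". Until then, "the research trial nurse will be unaware of group allocation until receiving confirmation for each participant". Next, "The tele-trial research nurse will then inform the people in custody and the custodial health nurses of treatment allocation". The section keeps the data manager/statistician masked but says openly of the allocation that "it will not be masked to the custodial health nurses and research trial nurse who will collect the baseline, post-intervention, and follow-up outcome data". It gives no reason for leaving the assessor unmasked.

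Recruitment states that "the tele-trial nurse will be responsible for data collection including key outcome measures and interviews" and describes this nurse as external to the prison health service. Clinical outcome measure- depression defines the first clinical outcome as "a change in depressive symptoms as assessed by the tele-trial research nurse using the PHQ-9 scale". The SF-36 section names no administrator, so Recruitment and the blinding section supply the role.

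The protocol uses several titles for this nurse (tele-trial nurse, research tele-trial nurse, research trial nurse). Their duties overlap so closely that I read them as one role.

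**The concern.** The assessor of the main clinical outcome starts out masked and is then unmasked by the plan's own procedure, for every participant and before any follow-up measure. The PHQ-9 is described as assessed by this nurse on items graded from absent to severe, so how a question is put or an answer recorded can shift with knowledge of the arm.

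What is at stake is the effect estimate. Statistical analyses promises effect-size differences with 95% confidence intervals to both follow-ups, and a GEE of the preliminary effects of BA. The Discussion carries the effect size into planning of the full trial. Potential Conflict of Interest recognises that staff and investigators may favour a good result, but its safeguards (fidelity supervision, team members new to BA, a steering group) do not protect outcome assessment. A feasibility trial is also the place to learn whether assessor masking can be kept in prisons, and the plan as written would teach nothing about that.

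**Working it through.** There is no stated figure to reproduce. The check traces who knows the allocation, when, and why.

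**1. Path of the allocation**
- Baseline: the trial nurse collects the data and does not know the arm.
- Randomisation: the external service emails the arm to the trial nurse.
- Announcement: the trial nurse tells the participant and the custodial nurses.
- Post-intervention and follow-up: the trial nurse collects the outcomes knowing the arm.

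The unmasking at the second step is certain and covers all of the planned 60 participants.

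**2. Who has to know**
- Custodial health nurses: yes. They deliver BA (Intervention) and are already told every allocation.
- Data manager/statistician: no. They could not take the email without losing their own masking.
- Trial nurse: no treatment task is listed. The first task that reveals the arm by its nature is the interview about experience of BA (Process evaluation).

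Sending the email to the custodial nurse therefore widens nobody's knowledge. It adds no selection bias either, because the external service fixes the allocation, after baseline, before anyone is told.

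**3. Routes that rerouting the email leaves open**
- Contextual factors: the trial nurse talks with custodial nurses and unit managers at baseline and at 6 weeks post-intervention. The stated content is about the site (organisational and staffing changes), but nothing rules out talk of individual participants.
- Interviews: Recruitment places them at the end of the study, with no rule that a participant's interview follows that participant's last PHQ-9 and SF-36.
- Disclosure: participants know their arm, and nobody is asked to withhold it from the trial nurse.

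**4. Self-completion**
Entry requires that participants "Understand, read, write, and speak English", so they can fill in the PHQ-9 and SF-36 themselves. This reduces the assessor's influence on the scores even where masking fails.

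**5. What is affected**
- Feasibility proportions (agreement, randomisation, session completion, follow-up completion) are counts and depend little on assessor masking.
- Effect sizes on PHQ-9 and SF-36 are exposed. With 30 per arm, the approximate 95% half-width of a standardised difference at one time point is 1.96 × √(1/30 + 1/30) = 1.96 × 0.258 = 0.51 SD, assuming all 60 are analysed without adjustment. That interval covers sampling error only and does not allow for a shift caused by an unmasked assessor.

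**The case against.** The strongest case against has four parts.

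- **The weakness is disclosed and lies outside the main purpose.** Statistical analyses makes the primary analysis descriptive and about feasibility, and the abstract says changes over time will be reported without judging them. This stands, and it limits the weight of the point. Disclosure is not a justification, though, and the effect size is still put to use in planning.
- **The gain is limited.** Both measures come from participants' answers, and participants stay unmasked. Self-completion would reduce the assessor's role whether or not the email is rerouted. This also stands. Rerouting and self-completion work together, and neither removes participant response bias.
- **Custodial nurses may lack capacity.** Limitations anticipates staff shortages, and the protocol says nothing on spare time. That these nurses can announce allocations is an inference, but a modest one, since they already screen and inform potential participants.
- **Treating staff are invested in the result,** as Potential Conflict of Interest admits. They would only be announcing an allocation already fixed and already known to them, and recruitment and consent would stay with the external nurse.

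A reader might infer that the email is the only cause of unmasking and that rerouting it would mask the assessor. The documents do not support this: the contextual conversations, the interviews and participant disclosure are further routes.

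**Conclusion.** The point holds as a cheap improvement. It is neither a contradiction nor an error in the plan. Receiving and announcing the allocation is the main avoidable source of assessor unmasking, and it can bias the between-arm effect sizes. The conclusion rests on reading the nurse's several titles as one role, and on custodial nurses being able to take on a small task.

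The size of the bias is unknown. A reader might put a number on it by assuming, for instance, a one-point PHQ-9 shift, or a true effect of 0.4 SD observed as 0.6 SD, which would size the next trial at (0.4/0.6)² = 44% of what it needs. The protocol supports neither. It gives no assessor effect and no PHQ-9 standard deviation, and the Discussion uses this trial's effect size together with those of other studies, so an error in it would not pass straight into the sample size.

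**What to change.** **In Random treatment allocation and blinding**
- Have the randomisation service send the allocation to the site's custodial health nurse, who tells the participant.
- Send the trial nurse only confirmation that randomisation is complete. The trial nurse stays masked until the participant's 3-month assessment is done.
- Reword the sentence on masking so that it is clear that only the trial nurse collects outcomes. As written, it could be read to include the custodial nurses.

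**In the clinical outcome sections**
- Have participants complete the PHQ-9 and SF-36 themselves.
- Ask participants and site staff not to tell the trial nurse the arm.
- Limit the contextual conversations to site-level information.
- Hold each participant's interview after the 3-month forms.
- Record the trial nurse's guess of the arm, so that the trial shows how well masking held.

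**Cost.** Protocol wording, a change in who receives the allocation (to be confirmed with the service, since the protocol does not describe its routing options), one extra data item, and a small added task for custodial nurses. No additional assessor is needed. Masking will be only partial, because participants know their arm and may disclose it. The report should say so and should note that participant response bias remains.
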